##### Analysis of the secondary outcomes

The analysis of the secondary outcomes will be the similar to the analysis of the primary outcome. We will estimate the difference between the groups using logistic regression, report odds ratios with 95% confidence intervals and their *p* values. All regressions will be adjusted for the pre-specified covariates as above (although with the acceptability of individual methods, the outcome at baseline will replace acceptability of effective contraception).

##### Analysis of the process outcomes

The process outcomes perceived norms, personal agency and intention are comprised of ordinal scales. Each scale will be analysed individually using ordered logistic regression to estimate proportional odds ratios. For knowledge, each correct answer will receive 1 point. The points will be summed and an overall score will be produced. We will use linear regression to test for a difference in mean scores between the arms.

To assess the ‘dose’ of the intervention that the intervention participants received, we will analyse the number of messages that participants reported to have read (all, most, some, none) and whether they stopped the messages. This will be reported descriptively.

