### Outcomes

#### Primary outcome

The primary outcome is the proportion of participants reporting that at least one method of effective contraception is acceptable at four months post randomisation. The acceptability of each method is binary (acceptable/not acceptable), but is derived from ordinal data from the following stems: Using the [method]… causes infertility, …causes unwanted side effects, …is easy, …is a good way to prevent pregnancy and I would recommend the [method] to a friend. The IUD and implant include an additional stem: The [method] insertion would not be a problem for me. The response options for each scale are: strongly disagree, disagree, not sure, agree, strongly agree and I do not know what the [method] is. A method is acceptable if participants report ‘agree’ or ‘strongly agree’ for all scales except for ‘…causes infertility’ and ‘…causes unwanted side effects’ stems, for which ‘disagree’ or ‘strongly disagree’ denotes acceptability (items 1-27 in Additional file 1 and items 4-30 in Additional file 2).

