##### Process outcomes

The process outcomes are: knowledge of effective contraception; perceived norms and personal agency in relation to using and communicating with partners about contraception; intention to use effective contraception and intervention dose received.

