### Baseline data collected

At baseline we will measure the primary outcome and collect the following personal and demographic data: full name; mobile phone number; email address; date of birth; marital status; number of children; residence; occupation; education level; current pregnancy intention; current method; how they heard about and enrolled in the study and the time that they prefer to receive the messages (see Additional file 1).

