### Follow-up data collected

At 4 months, we will measure the primary, secondary and process outcomes and collect the following data: if participants report using an effective method, where they obtained it; current pregnancy intention; whether they knew someone else that took part in the study and, if so, if they read each other’s messages (contamination); if they have experienced physical violence since being in the study and if anything good or bad happened as a result of receiving the messages (see Additional file 2). Staff unaware of partcipants’ allocation will contact participants by phone to collect the follow-up data (participants can also complete the questionnaire online or attend the service). For participants who report use of effective contraception at follow-up, local research staff will attempt to locate the service records to objectively verify use.

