##### Analysis of the primary outcome

The primary outcome is binary and we will compare the crude proportion reporting that at least one method is acceptable in each group. We will estimate the difference between the groups using logistic regression and will report the odds ratio along with the 95% confidence interval and its *p* value for evidence against the absence of intervention effect from the model. The primary analysis regression will be adjusted for baseline covariates likely to be associated with the outcome in order to improve the efficiency of the analysis and avoid chance imbalances [72]. These pre-specified covariates that we will adjust for are: pregnancy intention (wants to avoid/other); age (18–19/20–24 years); number of children (0/1+); highest education level completed (university/other) and acceptability of effective contraception at baseline (at least one method acceptable/no methods acceptable). We will also report the crude odds ratio between arms.

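### The process-outcome regressions are specified without the baseline covariates used in the primary, secondary and sensitivity analyses

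*Protocol article*

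**What the plan says.** The section Process outcomes lists knowledge, perceived norms and personal agency, and then "intention to use effective contraception and intervention dose received". Under Analysis of the process outcomes, norms, agency and intention are handled scale by scale: "Each scale will be analysed individually using ordered logistic regression to estimate proportional odds ratios". Knowledge is a sum of correct answers, and "We will use linear regression to test for a difference in mean scores between the arms". Dose is only described. No covariates are mentioned for any of these models.

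The neighbouring sections do mention them. Analysis of the primary outcome adjusts for pregnancy intention, age group, number of children, education and baseline acceptability, "in order to improve the efficiency of the analysis and avoid chance imbalances". Analysis of the secondary outcomes states "All regressions will be adjusted for the pre-specified covariates as above", with a swap of the baseline acceptability term for individual methods. Sensitivity analyses repeats the adjustment for both analyses it describes. Missing covariates says the database will not allow randomisation with an incomplete baseline questionnaire.

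On timing, Baseline data collected says "At baseline we will measure the primary outcome and collect the following personal and demographic data", and none of the process outcomes is in the list that follows. Follow-up data collected says "At 4 months, we will measure the primary, secondary and process outcomes and collect the following data".

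**The concern.** The Discussion relies on the process outcomes for evidence on the psychological processes through which the messages are meant to work. Three things are lost if these models carry only the treatment arm.

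1. **Precision.** Any baseline variable that predicts the outcome would shrink the residual variance at no cost in data collection. The primary analysis is adjusted for this reason and to deal with chance imbalance. Both reasons apply here too, and the article gives none for treating the process outcomes differently.
2. **The missing-data assumption.** Assumptions about missing data justifies the complete-case analysis as missing at random given the baseline covariates in the model. With no covariates, the conditioning set shrinks to the trial arm, and 20% loss to follow-up is anticipated. If education or age, say, predicts both dropout and knowledge, an adjusted model allows for it and an arm-only model does not.
3. **Comparability.** Odds ratios are non-collapsible. An arm-only proportional odds ratio is marginal, while the adjusted primary and secondary odds ratios are conditional on the covariates. Setting them side by side mixes two estimands.

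**Working it through.** **Step 1: reading the text.** Adjustment is stated in three places (primary, secondary, sensitivity) and is absent in one (process). The phrase in "All regressions will be adjusted for the pre-specified covariates as above" stands under the secondary-outcome heading, and the article keeps process outcomes apart from secondary ones in the Abstract, in Outcomes and in Follow-up data collected. General statistical considerations presents the text as the plan that the analysis will follow. The natural reading is that the process models are unadjusted, although the section does not say so outright.

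**Step 2: the plan's own sample size.** Inputs from Sample size: 50% v 65%, 90% power, with two-sided 5% from General statistical considerations.

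n per arm = [z(0.975)·√(2·p̄·(1−p̄)) + z(0.90)·√(p1(1−p1) + p2(1−p2))]² / (p2−p1)², with p̄ = 0.575

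= [1.960·√0.48875 + 1.282·√0.4775]² / 0.15² ≈ 226.2, rounded up to 227 per arm, or 454 in total, as stated. Then 454/0.80 = 567.5, so 568, against the 570 stated. The plan's figures reproduce. It gives no power for the process outcomes, so 227 per arm is carried over to them as an assumption.

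**Step 3: what adjustment would gain for the knowledge score.** R2 is the share of within-arm variance explained by the baseline covariates. It is not in the documents, so a range is assumed. For the linear model:

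- ratio of standard errors, adjusted to unadjusted = √(1−R2)
- detectable difference at 90% power, in unadjusted SDs = (1.960 + 1.282)·√(1−R2)·√(2/227)
- unadjusted sample size giving the same precision = 454/(1−R2)
- power when adjusted, for the difference of 0.263 SD that has 80% power unadjusted: (1.960 + 0.842)·√(2/227) = 0.263

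| Assumed R2 | SE ratio | Detectable difference (SD) | Power at 0.263 SD | Equivalent N |
|---|---|---|---|---|
| 0 | 1.000 | 0.304 | 80% | 454 |
| 0.05 | 0.975 | 0.297 | 82% | 478 |
| 0.10 | 0.949 | 0.289 | 84% | 504 |
| 0.20 | 0.894 | 0.272 | 88% | 568 |
| 0.30 | 0.837 | 0.255 | 92% | 649 |

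Inverting the ratio at the ends of the range: 1/0.975 = 1.03 and 1/0.837 = 1.19 to 1.20, so the unadjusted standard error is about 3% to 20% larger.

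**Step 4: the ordinal scales.** The residual-variance formula does not carry over to ordered logistic regression, where adjustment also changes the quantity estimated. No figure is offered for norms, agency or intention.

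**The case against.** The strongest reply is that the section is silent and does not declare a choice. It names model families and never calls them crude, a word the article does use for the primary outcome's unadjusted odds ratio. A condensed article may leave a covariate list to a fuller plan that is not shown. That stands to a degree: the unadjusted reading is an inference. It is a strong one, because the article presents itself as the plan and writes adjustment out for every other tier of modelling. The covariates are also already defined and complete, so this is an improvement that can be named and not just absent detail.

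Three stronger readings are tempting and not supported.

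- A reader might infer that the unadjusted comparisons are biased by chance imbalance. Under individual 1:1 randomisation they are not, and their confidence intervals already allow for it. Only informative dropout could bias them.
- A reader might infer that measuring the process outcomes only at follow-up is an error. It is not: a randomised comparison needs no baseline value. The timing also rests on the text lists, because the schedule figure and the questionnaires are not shown.
- A reader might take the baseline answer "I do not know what the [method] is" as a ready measure of prior knowledge. It is offered on each of the five or six stems per method, so a count of unknown methods has no unique value when a woman's answers differ across stems. It shows awareness of a method, and the knowledge items cannot be seen to judge how far the two agree.

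It is also fair that the chosen covariates are all dichotomised and none measures knowledge, so the lower end of the R2 range may be the realistic one.

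**Conclusion.** The point holds as a minor inconsistency in the analysis specification. The process-outcome regressions are written without covariates, while the other regressions for outcomes in the plan use a fixed set that is complete for every woman. The comparisons remain valid under randomisation. The cost is some precision, a missing-data assumption that conditions on arm alone, and odds ratios not directly comparable with the primary and secondary ones.

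The size of 3% to 20% on the standard error applies to the knowledge score only. It rests on an assumed R2 of 0.05 to 0.30 and on 227 women per arm with data. The primary result and its sample size are untouched.

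**What to change.** In Analysis of the process outcomes, state that the ordered logistic and linear regressions are adjusted for the covariates listed under Analysis of the primary outcome. If unadjusted models are intended, say so and give the reason.

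A baseline count of methods that the woman does not know may be added to the knowledge model. It is optional and needs a written rule for answers that differ across the stems of one method.

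The cost is one sentence, settled before the data are unmasked. No new assessment is needed, since every variable is collected before randomisation.

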#### Additional analyses

##### Sensitivity analyses

We will conduct sensitivity analyses regarding the missing data assumptions. In the first sensitivity analysis, we will consider that data are not MAR, and that all participants lost to follow-up did not find at least one method acceptable. In the second, we will adjust for the main baseline predictors of missingness. Both sensitivity analyses will be adjusted for the pre-specified covariates as above.

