### Sample size

The trial is powered to detect an increase in acceptability of effective contraception. Four hundred and fifty-four participants will allow for 90% power to detect a 15% absolute increase in acceptability, assuming 50% acceptability in the control group (i.e. 50% in the control vs. 65% in the intervention, corresponding to an odds ratio of 1.86). The sample size was calculated using the statistical software Stata 15.0 (syntax: power twoproportions .50 .65, test(chi2) power(0.9)) [68]. A 50% acceptability baseline is used in the absence of published data on acceptability in this context. If the actual baseline acceptability is higher or lower than 50%, the trial is still sufficiently powered to detect an absolute difference of 15%. For example, if the proportion in the control arm is 75%, there will be 90% power to detect an absolute difference of 12% (corresponding to 87% acceptability in the intervention group and an odds ratio of 2.23). Allowing for 20% loss to follow-up, 570 people will be randomised.

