### Analyses

#### General statistical considerations

The analysis of the data will follow the plan specified below. There will be no interim analyses and, therefore, no stopping rules. All analyses will be according to randomised arm and only participants with complete outcome data will be included in the primary analysis (a complete case analysis). All statistical tests will be two-sided. All effect estimates will be reported with a 95% confidence interval and its associated *p* value. Statistical significance will be considered at the 5% level. Analyses will be conducted using the latest version of Stata.

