#### Assumptions about missing data

As we are not aware of similar trials, it is not possible to investigate the pattern of missing data. The complete case analysis assumes that missing data for participants who did not complete follow-up are similar to data from participants who did complete follow-up, conditionally on baseline covariates included in the analysis model (i.e. that data is missing at random (MAR)) [69]. If participants who complete follow-up are more likely to find an effective method acceptable compared to those that are lost to follow-up, the observed proportion may overestimate acceptability [69]. European Union guidance on missing data in clinical trials highlights this limitation of MAR among others [70]. The guidance states, however, that ‘under reasonable assumptions’ the estimate of treatment effect is unlikely to be biased ‘to an important degree’. We will conduct the principal analysis under a MAR assumption (conditionally on the adjustment variables in the model), then perform sensitivity analysis under different assumptions for the missing data, as explained below.

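### The two missing-data sensitivity analyses are too narrow to show that the treatment effect is robust: neither lets the departure from MAR differ by arm, and the first moves with retention by arm

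*Protocol article*

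**What the plan says.** All references are to the protocol article.

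- General statistical considerations: the primary analysis is by randomised arm and restricted to women with complete outcome data.
- Assumptions about missing data: the primary analysis is MAR given the covariates in the model. The authors undertake to "perform sensitivity analysis under different assumptions for the missing data". Their stated worry is that completers may be more accepting than women who are lost, so that acceptability is overestimated.
- Sensitivity analyses: the first, declared not MAR, takes it that "all participants lost to follow-up did not find at least one method acceptable". It makes no distinction by arm. "In the second, we will adjust for the main baseline predictors of missingness". Both keep the pre-specified covariates.
- Loss to follow-up: loss is compared between arms by a chi-squared test, predictors of loss are reported, and their interaction with arm is tested.
- Sample size: 20% loss is allowed for, and 570 women are randomised.

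**The concern.** The stated worry concerns the level of acceptability. The trial's conclusion rests on the difference between arms, and that is biased when women are lost for different reasons, or in different numbers, in the two arms.

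The protocol gives grounds to expect this. The intervention arm receives 113 or 120 messages, mostly on contraception, and the control arm 16 about participation. Participants soon know their allocation. Under Participants' rights and safety, a woman who withdraws is no longer followed up, so dislike of the messages can lead directly to a missing outcome.

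The first analysis imputes the same value in both arms, so it cannot represent lost intervention women who are less favourable than lost controls. With unequal retention its estimate also mixes the treatment effect with the retention gap. The second analysis still assumes MAR. A reader could therefore be reassured, or alarmed, for reasons that say little about robustness of the effect.

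**Working it through.** **Planning figures.** The protocol states that "Four hundred and fifty-four participants will allow for 90% power to detect a 15% absolute increase in acceptability", with "50% in the control vs. 65% in the intervention, corresponding to an odds ratio of 1.86". Tests are two-sided at 5%. The usual two-proportion formula gives

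n per arm = [1.96·√(2×0.575×0.425) + 1.2816·√(0.50×0.50 + 0.65×0.35)]² / 0.15² = (1.370 + 0.886)² / 0.0225 ≈ 226.2, so 227 per arm and 454 in total.

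The odds ratio is (0.65/0.35)/(0.50/0.50) = 1.857. Dividing by retention, 454/0.8 = 567.5, stated as 570. These figures reproduce and are not in dispute. They give 285 randomised per arm and, at 20% loss, 57 lost and 228 completers per arm.

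**First analysis.** Arm proportion = completer rate × retention, with denominator 285. Odds ratios are crude, with Wald intervals; the protocol would adjust for covariates. Only the 20% average loss comes from the protocol; the unequal splits are assumptions that average 20%.

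| Completers C / I | Loss C / I | Analysed C / I | OR (95% CI) | p |
|---|---|---|---|---|
| 50% / 65% | 20% / 20% | 40.0% / 52.0% | 1.63 (1.17–2.27) | 0.004 |
| 50% / 65% | 15% / 25% | 42.5% / 48.8% | 1.29 (0.93–1.79) | 0.13 |
| 50% / 65% | 25% / 15% | 37.5% / 55.2% | 2.06 (1.47–2.88) | <0.001 |
| 50% / 50% | 20% / 20% | 40.0% / 40.0% | 1.00 (0.72–1.40) | 1.00 |
| 50% / 50% | 30% / 10% | 35.0% / 45.0% | 1.52 (1.09–2.13) | 0.015 |

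At equal loss the difference is 0.8 × 15 = 12 points whatever common rate is imputed. Setting all lost women to 0% gives 52% v 40%; setting them all to 50% gives 62% v 50%. Both odds ratios are 1.63.

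**Second analysis.** Suppose there is no missing-data bias and one independent prognostic covariate is added, with marginal rates held at 50% and 65%. Solve for a and b so that the average of expit(a + s·X) is 0.50 and the average of expit(a + b + s·X) is 0.65, with X standard normal. The conditional odds ratio exp(b) is 1.87, 1.92, 2.00 and 2.11 for s = 0.25, 0.5, 0.75 and 1.0, against 1.857. The shift runs from 1.874/1.857 − 1 ≈ 1% to 2.109/1.857 − 1 ≈ 14%. A binary covariate of 50% prevalence with odds ratio 2, 3 or 5 gives 1.89, 1.95 or 2.05.

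**The case not examined.** Completers are at 50% v 65%, with 57 lost per arm. Lost controls stay at 50%, and lost intervention women are at q. The intervention proportion is (0.65×228 + q×57)/285.

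Counting imputed outcomes as observed (n = 285 per arm):
- q = 65%: 65% v 50%, OR 1.86, p = 0.0003
- q = 50%: 62% v 50%, OR 1.63, p = 0.004
- q = 30%: 58% v 50%, OR 1.38 (0.99–1.92), p = 0.056
- q = 0%: 52% v 50%, OR 1.08, p = 0.63

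The unpooled z for the difference is 2.17 at q = 35% and 1.92 at q = 30%.

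That overstates the information, which comes from 228 completers per arm. With a fixed log-odds shift, the intervention estimate has variance [0.8 + 0.2·q(1−q)/(0.65×0.35)]² × 0.65×0.35/228.
- q = 35%: the bracket is 1, the variance 0.000998, and the control variance 0.25/228 = 0.001096. SE = √0.002094 = 0.0458, so z = 0.09/0.0458 = 1.97.
- q = 30%: the bracket is 0.985, SE = 0.0454, so z = 0.08/0.0454 = 1.76.

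The tipping point is therefore about 30% by the crude count and about 35% under delta-adjusted imputation.

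**The case against.** A reader might infer that the two analyses cannot test the result at all. The documents do not support that. The first is openly a non-MAR scenario and can change the conclusion: at 15% / 25% loss the effect is no longer significant, though its direction is unchanged. At equal loss it keeps a null effect null and shrinks a real one. The protocol does not call it a conservative bound, so showing that it is not one refutes no claim.

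The second analysis does alter the assumption, because MAR is defined as conditional on the variables in the model and it enlarges that set. Its shift in odds ratio is modest. It is nil if the predictors of loss are already among the five covariates or are not prognostic.

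Retention would not drive the first analysis unseen. Loss by arm is reported and tested: 15% v 25% with 285 per arm gives z = 0.10/√(2×0.20×0.80/285) = 2.98. Message burden, if it matters, points to more loss in the intervention arm, where the first analysis pulls against the intervention. The protocol gives no reason for the reverse split, so the spurious effect at 30% / 10% is only an illustration. Burden is also softened: women may stop the messages and stay in follow-up, and staff try non-responders up to three times.

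All of this stands, and it limits the point. It does not supply the missing piece. Reporting loss by arm shows how many are missing, not how far their outcomes would have to differ by arm to change the conclusion. Imputation detail may belong in an analysis plan that is not shown, but the article fixes these two analyses itself.

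**Conclusion.** The point holds as one of narrow scope. The two analyses do not show robustness of the treatment effect, because neither considers a departure from MAR that differs by arm. The first gives an odds ratio anywhere from 1.29 to 2.06 for the same completer rates as loss moves from 15% / 25% to 25% / 15% (control / intervention). The second stays MAR and can differ from the primary odds ratio by about 1–14% for reasons unrelated to missing data. An effect of the planned size would lose significance if acceptability among lost intervention women fell to roughly 30–35% while lost controls stayed at 50%.

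These figures rest on the planning rates, 57 lost per arm for the tipping point, assumed unequal loss splits for the first analysis, and unadjusted calculation. The range for the second analysis assumes an added covariate with logit SD 0.25 to 1.0. The primary analysis and sample size are not called into question. This is a cheap improvement worth making.

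**What to change.** 1. Add multiple imputation of the primary outcome from arm, the primary model covariates (including baseline acceptability) and the baseline predictors of loss. Apply a log-odds shift to the imputed values, varied separately by arm, and report the shift at which the conclusion changes.
2. Keep the analysis that counts missing as not acceptable, labelled as one scenario and presented beside the loss by arm already planned under Loss to follow-up.
3. In place of, or beside, the second analysis, fit the unchanged primary model to the zero-shift imputations or with inverse-probability weights. The odds ratio compared with the primary result then conditions on the same covariates.

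The cost is revised wording and a little more programming and reporting. All the variables are already collected, so no new data are needed.
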